breastfeeding cessation or successful ART initiation for infants diagnosed with HIV infection. Using this approach, the *Tingathe* program has catalysed improvements in ART uptake (and uptake of other ARV prophylactic regimens prior to Option B+ introduction), facility-based delivery, infant PMTCT prophylaxis, and EID testing. Similarly, Partners In Health—Malawi/ Abwenzi Pa Za Umoyo (APZU), established a CHW program in 2006 to support primary care service delivery in rural Neno District. The APZU program employs over 700 trained CHWs district-wide who serve as health educators, accompany patients with HIV, TB and other maladies to health facilities, and strengthen linkages for patients to the formal health system, including for PMTCT services.

Mentor mothers are mothers living with HIV who are employed, trained, and supervised to support health workers in under-resourced health facilities to deliver services as part of the health care team. The impact of mentor mothers has been reported previously from PMTCT programs throughout SSA. In Zimbabwe, a MSF-managed program demonstrated that clients receiving mentor mother support were twice as likely to return with their infants for EID testing compared to unsupported clients. Clients interviewed in this program reported decreased stigma, greater empowerment, and increased agency to disclose their HIV status to their male partner(s) and successfully negotiate condom use. In Uganda, the mentor mother model improved 12-month ART retention for HIV-positive mothers at mothers2mothers-supported facilities compared to clinics without mothers2mothers (m2m) services (90.9% vs. 63.6%, respectively). Assessment of MTCT at the end of breastfeeding demonstrated a durable impact to the m2m model, with the rate of HIV acquisition among 18-month-old infants being 6.8% in m2m-supported facilities compared to 8.7% in facilities without m2m. In South Africa, the presence of mentor mothers yielded favourable results on process indicators for HIV status disclosure, clinic attendance, and safe breastfeeding practices. In Malawi, m2m manages mentor mothers in over 100 clinics nationally who lead group and individual counselling sessions to provide psychosocial support and health education to new mothers and pregnant women living with HIV.

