#### 6.4 Sample Size

After enumerating the full retrospective cohort, we will randomly select eligible HIV-positive women and their HEIs for our nested cohort. For this nested cohort, our sample size will be determined by a power calculation for our primary outcome of interest—maternal retention in care 12 months after ART initiation. For this calculation (*see summary in Table 2 below*), we assume that 75% of MIPs receive services from a CFL model of interest in our selected districts, and that approximately 73% of HIV-positive mothers receiving the SOC will be retained in care at 12 months post-ART initiation (based on the most recent, first quarter 2017 data from the Malawi national program). With a two-sided alpha of 0.05, we will have 80% power to detect a programmatically meaningful 8% difference in the proportion of mothers retained in care between those who do and do not receive CFL services by enrolling 894 mothers from CFL sites and 298 mothers from SOC sites into our nested cohort (for a total of 1,192 mothers). Assuming that approximately 75% of HIV-positive mothers in SOC sites will be virologically suppressed (a weighted composite of 88% suppression among the 73% of HIV-positive mothers in care and approximately 40% suppression among the 27% of HIV-positive mothers not in care), we will have 83% power to detect a 8% difference in the proportion of HIV-suppressed mothers between those who do and do not receive CFL services. Finally, assuming that we will enrol about one HEI for every mother in the nested cohort, and that 92% of all HEIs not receiving CFL services (i.e. receiving SOC) are alive and HIV-free at 12 months (based on published data that 7% of HEIs become HIV-infected by 12-months and 96% of HIV-exposed but *uninfected* infants are alive at 12 months), we will have 90%

power to detect a 5% difference in HIV-free survival between HEIs who do and do not receive CFL models of interest by recruiting 1,192 total HEIs..

| Table 2: Summary of power and sample size calculations for primary outcomes of interest. |                                 |                    |              |                                 |                                 |

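### The 90% power for infant HIV-free survival rests on a 97% alternative that the plan's own 96% survival input puts out of reach

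*Protocol*

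**What the plan says.** Section 6.4 of the protocol sizes the nested cohort on maternal 12-month retention, "With a two-sided alpha of 0.05", by "enrolling 894 mothers from CFL sites and 298 mothers from SOC sites into our nested cohort". It then gives power at those numbers for two further outcomes.

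- **Infant 12-month HIV-free survival.** The SOC value is 92%. It is attributed to a 7% infection risk by 12 months and to the input that "96% of HIV-exposed but *uninfected* infants are alive at 12 months". At 1,192 infants the plan claims 90% "power to detect a 5% difference in HIV-free survival between HEIs who do and do not receive CFL models of interest". Table 2 repeats 92%, 5% and 0.90 with 894 and 298 infants.
- **Maternal viral suppression.** The SOC value is 75%, "a weighted composite of 88% suppression among the 73% of HIV-positive mothers in care" and about 40% among the 27% not in care. The text says "we will have 83% power to detect a 8% difference in the proportion of HIV-suppressed mothers".

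Section 6.4 gives no derivation for the 5-point infant effect or the 8-point suppression effect. Only the 8-point retention effect is described as programmatically meaningful.

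**The concern.** An infant counted as alive and HIV-free must be both uninfected and alive. If 96% of uninfected infants survive, HIV-free survival is (1 − infection risk) × 0.96 and cannot exceed 96%. The powered alternative of 97% lies above that, so the stated power is attached to an effect that the plan's assumptions exclude.

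A reader of Table 2 would take the infant comparison to be the best powered of the three. If the result were null, 90% power would invite the conclusion that CFL does not improve infant outcomes, although the largest effects consistent with the planning values are detected with lower probability or require transmission to fall very far.

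**Working it through.** **Inputs (all section 6.4).** Two-sided alpha 0.05 (z = 1.96); n₁ = 298 SOC and n₂ = 894 CFL; SOC infant HIV-free survival 92%; effect 5 points; infection by 12 months 7%; survival of uninfected exposed infants 96%.

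**Formula.** Two-proportion normal test with continuity correction:

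power = Φ{[d − c − 1.96·SE₀] / SE₁}, where d = p₂ − p₁ and c = ½(1/298 + 1/894) = 0.00224. SE₀ uses the pooled proportion; SE₁ uses the separate proportions. Setting c = 0 gives the uncorrected figure. Clustering by site is ignored, as it is in the plan's own calculation.

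**Step 1: reproduce the plan.**

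| Outcome | Comparison | Corrected | Uncorrected | Plan states |
|---|---|---|---|---|
| Retention | 73% vs 81% | 0.801 | 0.822 | 0.80 |
| Suppression | 75% vs 83% | 0.826 | 0.846 | 83% in text, 0.80 in Table 2 |
| Infant | 92% vs 97% | 0.899 | 0.921 | 0.90 |

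For infants: pooled p = 0.9575, SE₀ = 0.01349, SE₁ = 0.01672, and (0.05 − 0.00224 − 1.96 × 0.01349)/0.01672 = 1.27, giving Φ = 0.899. The corrected test reproduces the plan, so the stated powers are right for the stated differences.

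**Step 2: the ceiling.** At zero infection, HIV-free survival = 1.00 × 0.96 = 96%. To reach 97% the infection risk would have to be 1 − 0.97/0.96 = −1.0%, which is impossible. Reaching 97% would need zero transmission and also a fall in deaths among uninfected infants from 4% to 3%.

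**Step 3: the baseline.** The stated inputs give 0.93 × 0.96 = 0.8928, or 89.3%, not 92%. From 89.3%, a 5-point gain reaches 94.3%, below the ceiling. It requires infection of 1 − 0.9428/0.96 = 1.8%, down from 7%, a relative reduction of (7 − 1.8)/7 = about 74%.

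**Step 4: power at attainable alternatives.**

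| Comparison | SE₀ | SE₁ | Corrected | Uncorrected |
|---|---|---|---|---|
| 92% vs 96% (4 points, zero transmission) | 0.01458 | 0.01703 | 0.71 | 0.75 |
| 89.3% vs 94.3% (5 points) | 0.01703 | 0.01953 | 0.77 | 0.80 |

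Neither reaches 0.90.

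**Step 5: viral suppression.** The plan's mixture is S = 0.88R + 0.40(1 − R), with R the retained proportion.

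- R = 0.73 gives 0.7504. R = 0.81, the powered retention alternative, gives 0.7888, a gain of 3.8 points. Power for that gain is 0.26 (0.29 uncorrected).
- S = 0.83 needs R = (0.83 − 0.40)/0.48 = 89.6%. With R = 0.81 it needs in-care suppression of (0.83 − 0.40 × 0.19)/0.81 = 93.1%.
- R = 1 gives 88%, so an 8-point gain lies within the model.

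**The case against.** The strongest reply is that section 6.4 states what can be detected at a sample size fixed by retention; it does not forecast effects. Nothing is miscalculated, and the outcome is secondary under section 7.1, although the Table 2 caption calls all three primary. That stands as far as it goes, but a detectable difference still has to be attainable under the assumptions printed beside it, and 97% is not.

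A second reply is that 96% is a background survival figure and not a cap under CFL. Section 3.0 describes community health workers in general as possibly counselling on breastfeeding and managing malaria, which could reduce deaths among uninfected infants. This is possible, but section 6.4 does not build such an effect into the 5 points.

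A third reply is that the strict impossibility comes from pairing 92% with 96%: from 89.3%, 5 points fits under the ceiling, and zero transmission from there would have power of about 0.97. This is correct, and it is why the baseline and the effect must be reconciled together. It does not rescue the 90%, because 5 points from 89.3% has 0.77 to 0.80.

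A reader might infer that the suppression effect is equally out of reach, with true power near 0.26. The documents do not support that. The mixture allows up to 88%, and 83% power is correct for 75% versus 83%. The 3.8-point figure holds only if CFL acts solely through an 8-point retention gain, which the plan does not say. Section 3.0 cites a Ugandan programme with retention of 90.9% versus 63.6%; that 27.3-point difference would give 0.48 × 27.3 = 13.1 points of suppression. The same section cites infant acquisition of "6.8% in m2m-supported facilities compared to 8.7% in facilities without m2m" at 18 months. It would be selective to read that one comparison as the effect expected here.

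**Conclusion.** The infant row is wrong as written. Its 97% alternative exceeds the 96% maximum implied by the plan's survival input, and 90% is not supported from 92% (at most 4 points, power 0.71 to 0.75) or from the 89.3% that the inputs yield (5 points, power 0.77 to 0.80). The conclusion assumes that CFL leaves survival of uninfected infants at 96%, and it uses the plan's group sizes and unclustered test.

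The suppression row stands: 8 points is not derived, but it is not ruled out. A reader might also infer that both outcomes should no longer be presented as powered comparisons. That would be a preference, not a correction. Section 7.2.2.1 already commits to risk differences and risk ratios with 95% confidence intervals, so a null result would be shown with its uncertainty. The primary calculation for retention is not affected.

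**What to change.** In section 6.4 and the infant row of Table 2:

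1. Reconcile the SOC baseline, the effect and the survival input. Either use 89.3%, or state the inputs that give 92%.
2. Replace 90% with the power at the reconciled values. For 5 points from 89.3% this is about 77% with continuity correction and 80% without.
3. State the transmission reduction the effect requires (7% to about 1.8% in that case). If CFL is also expected to reduce deaths among uninfected infants, state that assumption.

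For viral suppression, an optional sentence would suffice: under the plan's mixture an 8-point retention gain alone implies about 3.8 points of suppression (power about 0.26 to 0.29), so 8 points also needs a larger retention gain or higher suppression among women in care.

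The cost is one sentence and one table row, plus the optional note. The stated infant power becomes less favourable. The sample size is unchanged because retention determines it.

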#### **6.4.1 Sampling Approach for Facility Catchment Areas**

Across the 5 study districts, we have identified the characteristics of interest for sampling facility catchment areas to be the district and CFL model (or SOC). To recruit our study population, we will first enumerate all high-volume health facility catchment areas within these districts, where “high volume” is defined as  $\geq 30$  pregnant women newly diagnosed with HIV infection in the catchment area within the last year. We will confirm the CFL model of interest/ SOC active in each facility catchment area prior

to data collection during the study start up phase through consultation with CFL programme managers /directors and District Health Offices (DHOs).

We will then stratify all facility catchment areas according to both district (i.e. 5 districts) *and* CFL model/ SOC (i.e. 4 total models) to create 20 “joint strata”. Within each district, we will randomly select a fixed proportion (ranging between 66% and 100%) of high-volume facility catchment areas to identify approximately **40 facility catchment areas** that will serve as study sites. Table 1 provides an example of our approach to sampling community facility catchment areas within the districts of interest. A minimum of two facility catchment areas (“clusters”) per stratum will be needed to quantify the within and between cluster variability in outcomes of interest (i.e. “rate of homogeneity”), and to provide overall variance and precision estimates. This sampling strategy serves as the starting point for recruiting the study population.

| Table 1: Illustrative sampling approach for study sites.  |                                                                   |                             |                                                             |
|------------------------------------------------------------------|-------------------------------------------------------------------|-----------------------------|-------------------------------------------------------------|
| District                                                  | CFL Model (SOC=0, Mentor Mother=1, Expert client=2, CHW=3) | Joint stratum number | Estimated Number of Sampled Facility Catchment Areas |
| 1 (Salima, total 6 high-volume sites, 100% sampled)              | 0                                                                 | 1                           | 0                                                           |
| 1 (Salima)                                                       | 1                                                                 | 2                           | 0                                                           |
| 1 (Salima)                                                       | 2                                                                 | 3                           | 0                                                           |
| 1 (Salima)                                                       | 3                                                                 | 4                           | 6                                                           |
| 2 (Lilongwe, total 12 high-volume sites, 75% sampled)            | 0                                                                 | 5                           | 2                                                           |
| 2 (Lilongwe)                                                     | 1                                                                 | 6                           | 3                                                           |
| 2 (Lilongwe)                                                     | 2                                                                 | 7                           | 2                                                           |
| 2 (Lilongwe)                                                     | 3                                                                 | 8                           | 2                                                           |
| 3 (Mzimba North/ South, total 7 high-volume sites, 100% sampled) | 0                                                                 | 9                           | 2                                                           |
| 3 (Mzimba North/South)                                           | 1                                                                 | 10                          | 4                                                           |
| 3 (Mzimba North/South)                                           | 2                                                                 | 11                          | 2                                                           |
| 3 (Mzimba North/ South)                                          | 3                                                                 | 12                          | 0                                                           |

|                                                                                                                                                                            |   |           |           |
|----------------------------------------------------------------------------------------------------------------------------------------------------------------------------|---|-----------|-----------|
| 4 (Neno, total 5 high-volume* sites, 100% sampled)                                                                                                                         | 0 | 13        | 0         |
| 4 (Neno)                                                                                                                                                                   | 1 | 14        | 0         |
| 4 (Neno)                                                                                                                                                                   | 2 | 15        | 0         |
| 4 (Neno)                                                                                                                                                                   | 3 | 16        | 5         |
| 5 (Zomba, total 16 high-volume sites, 81% sampled)                                                                                                                         | 0 | 17        | 2         |
| 5 (Zomba)                                                                                                                                                                  | 1 | 18        | 3         |
| 5 (Zomba)                                                                                                                                                                  | 2 | 19        | 6         |
| 5 (Zomba)                                                                                                                                                                  | 3 | 20        | 2         |
| TOTAL                                                                                                                                                               |   | 20 | 40 |
| *Due to the highly rural and dispersed population in Neno, “high-volume” will be more than 10 pregnant women newly diagnosed in the catchment area within the past 1 year. |   |           |           |

As described in further detail below (see section 6.5.1), CFL site assessments will be conducted at about 20 purposively selected facility catchment areas where MOH PMTCT services are available and where one of the three CFL models of interest, or the SOC, are being offered.

To successfully meet our nested cohort enrolment target (accounting for missing locator information, maternal death, and other enrolment barriers), we will randomly sample at least 30 HIV-positive mothers per site from a fully enumerated list of all HIV-positive women meeting eligibility criteria, and seek to recruit a final nested sample of approximately 1,200 HIV-positive mothers and their HEIs (~30 MIPs per site x ~40 sites) from across all study sites. Based on Malawi HIV Unit program data, we anticipate that about 30 randomly selected HIV-positive mothers per site will represent a sample of between approximately 15% to 100% of all HIV-positive mothers newly enrolled into PMTCT during the full cohort period at each site, depending on PMTCT client volumes at selected facility catchment areas. This nested cohort sample size will not only allow for site-specific revised estimates of patient outcomes, but will also contribute site-level data to generate overall estimates for the full cohort for each CFL model.

To arrive at projected weights for each observation in our sampling scheme—which vary across joint strata—we have made the following assumptions: 1) at the *time of construction of the full MIP cohort*, we anticipate that approximately 73% of HIV-infected mothers will be alive and in care, with 4% documented as having transferred out, stopped ART, or died, and another 23% documented as lost to

follow-up (LTFU) to the national PMTCT/ART program (defined by the MOH as all those who have not returned to the clinic for more than 2 months after the date when they were expected to run out of antiretrovirals and are not documented as having transferred out, stopped ART, or died); 2) mortality is 30% among HIV-infected mothers who are LTFU; and 3) a coefficient of variation of 0.15 should be adequate to obtain relatively conservative projections of precision in each joint stratum. Applying these considerations to our MIP target population, we will select between 66% and 100% of high-volume sites and about 30 MIPs at each site from across the 20 joint strata to enrol our nested cohort (**Table 3**).

**Table 3:** Illustrative sampling approach for individual mother-infant pairs at facility catchment area level.

| Joint stratum number | Total high-volume catchment areas in strata | Expected catchment areas sampled (66 - 100%) | Expected Range of number of PMTCT mothers available for sampling per joint stratum | Approximate Total Mothers sampled | Approximate Mothers with complete routine care data (.73 SOC, .80 CFLs) | Approximate Mothers Needing Tracing (0.27 SOC, 0.20 CFLs) |
|----------------------|---------------------------------------------|----------------------------------------------|------------------------------------------------------------------------------------|-----------------------------------|-------------------------------------------------------------------------|-----------------------------------------------------------|
| 1*                   | 0                                           | 0                                            | 0                                                                                  | 0                                 | 0                                                                       | 0                                                         |
| 2                    | 0                                           | 0                                            | 0                                                                                  | 0                                 | 0                                                                       | 0                                                         |
| 3                    | 0                                           | 0                                            | 0                                                                                  | 0                                 | 0                                                                       | 0                                                         |
| 4                    | 6                                           | 6                                            | 300 - 400                                                                          | 180                               | 144                                                                     | 36                                                        |
| 5*                   | 2                                           | 2                                            | 80 - 100                                                                           | 60                                | 44                                                                      | 16                                                        |
| 6                    | 4                                           | 3                                            | 400 - 500                                                                          | 90                                | 66                                                                      | 24                                                        |
| 7                    | 2                                           | 2                                            | 150 - 200                                                                          | 60                                | 48                                                                      | 12                                                        |
| 8                    | 2                                           | 2                                            | 60 - 100                                                                           | 60                                | 48                                                                      | 12                                                        |
| 9*                   | 2                                           | 2                                            | 90 - 120                                                                           | 60                                | 44                                                                      | 16                                                        |
| 10                   | 4                                           | 4                                            | 100 - 200                                                                          | 150 #                  | 120                                                                     | 30                                                        |
| 11                   | 2                                           | 2                                            | 300 - 400                                                                          | 90 #                   | 72                                                                      | 18                                                        |
| 12                   | 0                                           | 0                                            | 0                                                                                  | 0                                 | 0                                                                       | 0                                                         |
| 13*                  | 0                                           | 0                                            | 0                                                                                  | 0                                 | 0                                                                       | 0                                                         |
| 14                   | 0                                           | 0                                            | 0                                                                                  | 0                                 | 0                                                                       | 0                                                         |
| 15                   | 0                                           | 0                                            | 0                                                                                  | 0                                 | 0                                                                       | 0                                                         |
| 16                   | 5                                           | 5                                            | 50 - 100                                                                           | 90 ^                   | 72                                                                      | 18                                                        |
| 17*                  | 2                                           | 2                                            | 60 - 100                                                                           | 60                                | 44                                                                      | 16                                                        |
| 18                   | 3                                           | 2                                            | 150 - 200                                                                          | 60                                | 48                                                                      | 12                                                        |
| 19                   | 9                                           | 6                                            | 900 - 1,100                                                                        | 180                               | 144                                                                     | 36                                                        |
| 20                   | 2                                           | 2                                            | 100 - 200                                                                          | 60                                | 48                                                                      | 12                                                        |
| Total         | 45                                   | 40                                    | 2,740 - 3,720                                                               | 1,200                      | 942                                                              | 258                                                |

\*Denotes SOC stratum (see Table 1 above)

#Denotes strata where over-sampling will take place to achieve balance across strata

^Lower estimated number of mothers sampled given highly rural population (see Table 1 above)

